**Methods/Design:**

This is a two-arm pilot cluster randomised controlled trial (RCT). We aim to recruit 300 parents with a diagnosis of PTSD. The screening will be done using the Impact of Event Scale-Revised. Diagnosis of PTSD will be confirmed using the Clinician-Administered PTSD Scale-5 (CAPS-5). Union Councils from Peshawar and Karachi will be randomised into either group LTP Plus TF CBT arm or treatment as usual (TAU). The intervention includes 12 sessions of LTP Plus TF-CBT delivered weekly in the first 2 months and then fortnightly in a group setting by trained psychologists. The groups will be co-facilitated by the community health workers (CHWs). Parents will be assessed at baseline and 4th month (end of the intervention), using the Patient Health Questionnaire (PHQ-9), Generalised Anxiety Disorder (GAD-7) Scale, Client Service Receipt Inventory (CSRI), and Ages and Stages Questionnaire (ASQ-3)

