## Method

### Design

This is a two-arm pilot cluster RCT. Both qualitative and quantitative assessments will be administered to all eligible participants at baseline and after 4 months (end of the intervention).

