### Randomisation

Randomisation will be computer-generated by an off-site statistician. The unit of a cluster will be Union Councils. A union council forms the second-tier of local government and fifth administrative division in Pakistan, The Union Councils will be randomly allocated to one of the two arms; arm-1 is the intervention group receiving LTP Plus and TF-CBT whereas Arm-2 is routine care.

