### Procedure

Trained CHWs will approach potential participants in community settings (e.g. primary care, basic health units) in both intervention and control clusters. CHWs will assess potential participants against eligibility criteria (accept the diagnosis of PTSD using CASP). All potentially eligible participants will be invited for a meeting with a trained researcher who will then administer CASP on otherwise eligible participants. After screening, a detailed Participant Information Leaflet (PIL) will be provided to eligible parents and written (thumb impression for participants who are unable to read and write) consent will be obtained. Trained researchers will complete baseline assessment with all consented participants. Participants in the intervention cluster will receive 12 group sessions of LTP Plus TF CBT over the period of 4 months. A follow-up assessment will be done with all the participants 4 months after baseline.

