### Sample size

To have an effect size of 0.45, assuming 5% significance level, 80% power and 10% drop out (Husain *et al*., 2017b) during the study, we need to recruit 300 parents. The objective for which the larger sample size is needed relates to the intra-cluster correlation coefficient (ICC), which measures the degree of similarity in outcome amongst parents in the same cluster; for this, the key is the number of clusters (Rutterford *et al*., 2015). Moreover, groups (and hence clusters) of size around 10 is the optimal size for interventions such as LTP Plus TF-CBT (Biggs *et al*., 2020). We propose a minimum of 15 clusters in each of the LTP + TF-CBT and routine care arms, in order to be able to obtain a relatively precise estimate of the ICC and to check whether it might be greater in the LTP + TF-CBT and routine care arms as the former may have additional variation due to the delivery of the group-based therapy. We, therefore, expect to recruit around 300 parents (approximately 10 each from 15 LTP + TF-CBT and 15 TAU clusters) which will enable the estimation of recruitment and retention rates with sufficiently good precision to inform a full effectiveness trial.

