### Statistical analysis plan

The study will be carried out in accordance with the CONSORT guidelines. All analyses will be based on the intention-to-treat sample and missing data will be imputed with multiple imputation procedures as implemented in Statistical Package for Social Sciences (SPSS) software (version 27). To assess the primary and secondary outcomes, a two-sided significance level of 0.05 will be employed to enable the detection of a difference between interventions in both directions. Demographics and baseline variables in the two study arms will be compared using various descriptive statistics of means, standard deviations, and proportions. For primary outcome analysis, a two-sample two-sided test of proportions will be used to compare the difference in the rate of PTSD (assessed using the CAPS-5) at 4-month post-randomisation between LTP Plus and TF-CBT and TAU groups. For the secondary analyses, we will compare the proportions similarly for binary outcomes and use tests for comparing means for the continuous outcome. Additionally, we shall use multivariable techniques in assessing the effect of various covariates including baseline measures on outcomes. If required appropriate transformation of continuous variables will be considered. ICC will be calculated to help future cluster-based research on this topic.

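### The one 4-month CAPS-5 assessment is timed from three different points, and the stated session schedule leaves only 7 to 24 days before it

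*Protocol article*

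**What the plan says.** All references are to the protocol article. There is one assessment after baseline, and its timing is given in four places:

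- **Abstract, Methods/Design:** "Parents will be assessed at baseline and 4th month (end of the intervention").
- **Design:** assessments "at baseline and after 4 months (end of the intervention").
- **Procedure:** "A follow-up assessment will be done with all the participants 4 months after baseline". The same section says the 12 group sessions are spread over 4 months.
- **Statistical analysis plan (primary analysis):** the arms are compared on "the rate of PTSD (assessed using the CAPS-5) at 4-month post-randomisation".

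Three other statements bear on whether these dates agree. Under Randomisation, "The Union Councils will be randomly allocated to one of the two arms", so the randomisation date belongs to the council. The Abstract describes "12 sessions of LTP Plus TF-CBT delivered weekly in the first 2 months and then fortnightly". Sample size treats "groups (and hence clusters) of size around 10" as the optimal size, which implies one therapy group per council.

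**The concern.** The primary endpoint has three clocks: the parent's baseline, the end of the course, and randomisation. In an individually randomised trial these might nearly coincide. Here randomisation is an event of the council, baseline is an event of the parent (after screening, diagnostic interview and consent), and session 1 is an event of the group. Staff could schedule visits from different clocks while each followed the text.

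The course takes up almost the whole 4 months, so there is little room for a gap between baseline and session 1. Parents assessed before the last session would be compared with TAU after only part of the programme, which would dilute the estimated effect. If councils differ in how long they take to start, the amount of treatment delivered by the assessment would also differ between councils, and only in the intervention arm. The Sample size section wants to learn whether the ICC is larger in the intervention arm because of group delivery. Variation caused by assessment timing could not be told apart from that.

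**Working it through.** **Inputs from the document.** Twelve sessions, weekly for 2 months and fortnightly afterwards; course length 4 months; follow-up at 4 months; groups of about 10. **Assumed, because the document does not say:** 8 or 9 weekly sessions in the 2 months; 4 months taken as 16 × 7 = 112 days or 4 × 30.4375 ≈ 122 days; the delay from baseline to session 1; the time a group takes to fill.

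**Step 1. Reproduce the stated course length.** Count session 1 as day 0.

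- 8 weekly sessions fall on days 0 to 49, then fortnightly on 63, 77, 91, 105. Session 12 is on day 105 (15 weeks).
- 9 weekly sessions fall on days 0 to 56, then fortnightly on 70, 84, 98. Session 12 is on day 98 (14 weeks).

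Both fit within 4 months, so the plan's own figure is reproduced.

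**Step 2. Slack if session 1 is on the day of baseline** (follow-up day minus day of session 12).

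- 8 weekly: 112 − 105 = 7 days; 122 − 105 = 17 days.
- 9 weekly: 112 − 98 = 14 days; 122 − 98 = 24 days.

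The slack is therefore 7 to 24 days, about 1 to 3.5 weeks.

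**Step 3. Sessions delivered by a baseline-anchored visit.** With a delay of d days from baseline to session 1, the visit falls on day 112 − d or 122 − d of the course.

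| Assumed delay | Sessions delivered, of 12 |
|---|---|
| 7 days | 12 |
| 14 days | 11 to 12 |
| 28 days | 10 to 11 |
| 42 days | 9 to 10 |
| 56 days | 8 to 9 |

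For example, a 56-day delay puts the visit on day 56 or 66. Counting session days up to then gives 8 or 9 sessions.

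**Step 4. Share of a group assessed before session 12.** Illustration only: 10 parents have evenly spaced baselines over F days, and session 1 is on the day of the last baseline. Parent i (i = 0 to 9) waits F × (1 − i/9) days and is affected if the wait exceeds the slack. A tie counts as completed.

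| Fill time F | Slack 7 | Slack 14 | Slack 17 | Slack 24 |
|---|---|---|---|---|
| 7 days | 0% | 0% | 0% | 0% |
| 14 days | 50% | 0% | 0% | 0% |
| 28 days | 70% | 50% | 40% | 20% |
| 42 days | 80% | 60% | 60% | 40% |
| 56 days | 80% | 70% | 70% | 60% |

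At F = 42 and slack 14 there is an exact tie: 42 × (1 − 6/9) = 14. Counting that parent as affected would give 70% and leaves the overall range unchanged.

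**Step 5. The randomisation clock.** If the council is randomised L days before session 1, a visit 4 months after randomisation falls on day 112 − L or 122 − L of the course for the whole group. With an assumed L of 60 days this is day 52 or 62, when 8 or 9 sessions have been delivered. If allocation instead came after the baselines, this clock would run later than the baseline clock.

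**The case against.** The Abstract, Design and Procedure can be read together as one nominal plan: a course of about 4 months, a visit at 4 months, and the end of the intervention as a label for that visit. With a prompt start, session 12 does come before the visit. This is fair, and it leaves the Statistical analysis plan as the plainest departure. But the label is true of a baseline-anchored visit only while the start delay stays inside the slack, and the primary analysis uses a third clock.

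A reader might infer that groups must fill before they start, and that many parents will therefore be assessed mid-course. The document does not support this. It gives about 10 as an optimal size, not a condition for starting, and states no recruitment rate, fill time or start delay. Baselines in a council could be done in a batch. On the 122-day count, a fill time of up to 17 days affects nobody under either schedule.

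A reader might also take it as settled that councils are allocated before parents are approached. Procedure describes recruitment in clusters already labelled by arm, which suggests that order but does not state it. Nor does the text support a claim that parents still attending sessions are more likely to unblind the assessor than parents who have just finished. Session completion is taken from session logs, so it does not depend on the assessment date.

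Visit windows and index dates are commonly left to a full protocol or analysis plan, so their absence here is not the point. The point is the conflicting wording. Finally, this is a pilot, so the effect estimate is preliminary. That limits the harm from dilution, but not the harm to the ICC comparison, which is one of the pilot's own aims.

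**Conclusion.** The point holds as an inconsistency in the timing of the primary endpoint, which needs no assumption: the same CAPS-5 assessment is tied to baseline, to the end of the intervention and to randomisation, and cluster randomisation means these dates can differ. All three put the visit after the last session only if council randomisation, baseline and session 1 fall within about 1 to 3.5 weeks of one another.

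The consequence is conditional. Parents whose session 1 comes later than that after baseline may be assessed before the course ends. The share cannot be computed from the document. Across the assumed fill times of 1 to 8 weeks it runs from 0% to about 80%, given even enrolment and a start on the day of the last baseline. If councils are in fact allocated before recruitment, a post-randomisation clock would bring the assessment earlier still.

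**What to change.** Use one anchor in the Abstract, Design, Procedure and Statistical analysis plan, and replace the post-randomisation wording in the last of these. Define the anchor by the same event in both arms, for example the date on which a council's enrolment or baseline assessments close. Using session 1 in intervention councils and close of enrolment in TAU councils would not do: any gap between the two would lengthen follow-up in one arm only.

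Assess every parent in both arms at the same fixed interval from the anchor. Choose the interval and window so that the visit falls after the last scheduled session, allowing for the gap expected between the anchor and session 1. Record for each parent the days from baseline to session 1 and from the last session to assessment, so that the pilot can report the delays that cannot be known now.

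The cost is protocol wording and visit scheduling, with no extra participants or visits. The downside is that parents who enrol early are followed somewhat longer from their own baseline. This applies in both arms, but is equal only if councils fill at similar speed in each arm, so fill time should be reported by arm.

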### Intervention

#### Learning through play + trauma-focused cognitive behaviour therapy (LTP + TFCBT)

The culturally adapted parent-focused group intervention (LTP plus TF-CBT) will be delivered to parents by masters-level trained psychologists supported by CHWs weekly during the first 2 months and then fortnightly at schools either at school drop-off or pick-up time depending on participant's preference and other community settings. The parenting component of the intervention (LTP) will be led by the CHWs and psychologists will lead the TF CBT component of the intervention. We have published a large cluster RCT of integrated parenting intervention called LTP Plus CBT for depressed mothers where CHWs successfully delivered intervention facilitated by the psychologists (Husain *et al*., 2021). The Intervention will be delivered in 12 sessions of 60–90 min in addition to routine care. The LTP plus TF-CBT has two components;
Culturally adapted learning through play (LTP)Culturally adapted trauma-focused cognitive behaviour therapy (TF-CBT)

LTP aims to enable parents to improve their child's psychical and psychosocial development by educating about child development and the importance of parent-child play. The pictorial calendar, which starts from birth and exhibits eight stages of healthy child development until 6 years of age, is an important feature of LTP. To enable a better understanding of how learning and attachment works, the calendar comes with culturally adapted illustrations of parent-child play (Husain *et al*., 2020).

Component 2 of this integrated group intervention involves a culturally adapted manual-assisted cognitive behaviour therapy (CBT) for PTSD, based on the cognitive model by Ehlers and colleagues (Ehlers *et al*., 2005). The cognitive appraisals, memory characteristics and behavioural strategies which maintain PTSD are all considered while developing this model. The aim is to encourage careful questioning to modify negative appraisals of the trauma. The culturally adapted manual BASID (Baad Az Sadma Zehni Dabao) Ki Kahani – The Story of Basid (Latif *et al*., 2020), consists of nine chapters and in addition to psycho-education and culturally sensitive advice on improving relationships, it includes practical exercises on; dealing with avoidance, behavioural activation, problem-solving and dealing with unhelpful ways of thinking through thought restructuring. The manual uses culturally sensitive idioms of distress, stories, and expressions. For example, the principle of exposure is explained through Aesops' famous fable about a lion who fears a lion in the water when he tried to drink water from a pond. It is only when he jumps over the lion that the lion disappears. The manual describes stories of three persons who have experienced trauma, and how they managed their traumatic stress.

Chapters of BASID are woven throughout the intervention curriculum, as evidenced from table 3, each session contains some content from LTP and some part from BASID. The first part of the session (approximately 30–40 min) is focused on LTP and the second part (approximately 40–50 min) is dedicated to parents' mental health using BASID chapters. Three stories ([name], [name] and [name]) are referred to throughout the different sections of BASID such as how Muhamad Sabir prepared a list of graded exposure (session 5), how Muhammad Sabir identified his problems in problem-solving session (session 8), Nasreen Bibi's thought diary and thought challenging in session 9 and 10, Rasheed's example in session 12 on staying healthy (Table 1).

**Table 1. tab01:** LTP Plus TF CBT Intervention schedules

Session number	LTP	TF-CBT
1	Orientation to the intervention programme, Introduction to group rules, structure of sessions, frequency and timing of sessions etc.	
2	Introduction of the LTP Calendar; Overview of 5 domains of development – Sense of self, Physical Development, Relationships, Understanding, and Communication	Introduction of the fundamental principles of CBT
3	The younger 3 years old: Things that a younger 3 years old child shall do, role of parents (e.g. staying nearby the child when he/she tries new things, sharing books with children, story-telling etc), offering opportunities to learn (climbing, jumping, matching games etc)	Psychoeducation: What is trauma, symptoms of PTSD, vulnerable groups through three local culturally relevant stories. Relaxation exercise
4	The Older 3 years old: Things an older than 3 years old child shall do with pictorial illustrations. Helping parents to learn how to provide stimulation to the child such as make-believe plays, playing outside, learning how to take turns etc.	Ways to deal with fear, fight and flight responses. Problems related to sleep. Sleep hygiene
5	The younger 4 years old: Things a younger 4 years old child shall do. Helping parents how to teach their child different ways to express their feelings, settings routine of a child, providing them information about different body parts etc.	Ways to deal with Fear – Introduction to the graded exposure, preparing fear hierarchy (list of feared objects, activities and situations), ranking difficulty. An example from manual to be used. Encouraging to start with mildly difficult exposure
6	The younger 4 years old: Helping parents to provide stimulation for child development such as sense of self (offering them choices), physical development (drawing), relationship (inviting friends to play with child), parents engaging child in a play.	Ways to deal with Fear – Graded exposure Introducing coping strategies (deep breathing, counting backward, reciting verses from the Holy Quran, etc)
7	The older 4 years old: Things that an older 4 years old child shall do. Educating parents to provide time and space to the child to play. Examples of some easy play activities, helping parents in ensuring safety of the child.	Psychoeducation of vicious Activity scheduling
8	The older 4 years old: Helping parents to provide stimulation for child development such as sense of self (importance of answering child's questions in an honest way), physical development (outdoor play), relationship (helping child to recognise others' feelings and responding to others feelings), rhymes.	Problem solving – identifying problems and mutually exploring potential solutions using an example from the manual. Learning the technique of cost/benefit analysis
9	The younger 5 years old: Things a younger 5 years old child shall do (pictorial illustrations). Helping parents to understand importance of assigning simple jobs to the child, educating child about family's rules and how to offer child ways to explore their environment.	Helping participants to talk about thoughts and emotions. Physical manifestation of symptoms (e.g. of anxiety, fear) CBT cycle Thought keeping Diary
10	The younger 5 years old: Helping parents to provide stimulation for child development such as sense of self (appreciating child on completion of simple tasks), physical development (e.g. building something), solving problems on their own, looking at the calendar etc.	Thought challenging and practicing alternative healthy thoughts Thought Diary
11	The older 5 years old: Things and older 5 years old child shall do (pictorial illustrations). Helping parents to understand certain facts such as giving child an opportunity to say ‘no’, importance of giving opportunity to the child to experiment with different activities, listening to the child's stories attentively etc.	Communication skills Anger Management
12	The younger 5 years old: Helping parents to provide stimulation for child development such as sense of self (encouraging child when he gets frustrated while doing complex activities), physical development (e.g. crafting), counting patterns, sharing jokes etc. Certificate Distribution	Tips to stay healthy later on

### Research assistant (RA) training and inter-rater reliability

Training sessions for assessment measures are conducted for the RAs in Pakistan by senior trained professionals (NH, ZZ, FN, NC). To ensure consistency, local principal investigators (PIs) will measure the inter-rater reliability throughout the study. Moreover, those who deliver the intervention will attend a 3-day training on LTP Plus TF CBT by master trainers. These training sessions will involve a structured presentation on each session from the manual followed by a role play and discussion. These interventionists will be regularly supervised by the master trainers (AQ, ZZ, TK). These supervision sessions will be held on a fortnightly basis and include role play, case presentations and discussions.

For assessment of fidelity, we will use the participant observation method that we have already used in our published cluster RCT (Husain *et al*., 2021). On each study site (Peshawar and Karachi) two senior raters expert in LTP plus TF CBT will attend the sessions as delegates. Raters will develop and use a specific observation checklist which will be comprised of different domains from each age range of LTP and from each area of development from five areas identified in the LTP manual, as well as core components of TF CBT. The two raters will independently rate each session. Scores on the observation checklist will be reviewed for assessment of fidelity. In order to ensure consistency, the same two raters on each site will complete the fidelity assessments.

#### Treatment as usual (TAU)

The TAU group will receive routine treatment which may consist of support from general practitioners. The TAU also includes routine care provided by the CHWs (called Lady Health Workers in Pakistan). The CHWs are responsible for maternal, neonatal and child health in Pakistan and also take care of immunisation and family planning. Each CHW is responsible for approximately 150 households and they visit each household once a month (visiting 5–7 homes daily). They are also trained in interpersonal communication and community engagement.

All the participants in the TAU group will also receive detailed baseline and follow up assessment visits.

